## Abstract

**Introduction:**

Healthcare-associated infections (HCAIs) are a major cause of morbidity and mortality in critically ill children. In critically ill adults, there are data that suggest the use of Selective Decontamination of the Digestive tract (SDD), alongside standard infection control measures reduce mortality and the incidence of HCAIs. SDD-enhanced infection control has not been compared directly with standard infection prevention strategies in the Paediatric Intensive Care Unit (PICU) population. The aim of this pilot study is to determine the feasibility of conducting a multicentre cluster randomised controlled trial (cRCT) in critically ill children comparing SDD with standard infection control.

**Methods and analysis:**

Paediatric Intensive Care and Infection Control is a parallel group pilot cRCT, with integrated mixed-methods study, comparing incorporation of SDD into infection control procedures to standard care. After a 1-week pretrial ecology surveillance period, recruitment to the cRCT will run for a period of 18 weeks, comprising: (1) baseline control period (2) pre, mid and post-trial ecology surveillance periods and (3) intervention period. Six PICUs (in England, UK) will begin with usual care in period 1, then will be randomised 1:1 by the trial statistician using computer-based randomisation, to either continue to deliver usual care or commence delivery of the intervention (SDD) in period 2. Outcomes measures include parent and healthcare professionals’ views on trial feasibility, adherence to the SDD intervention, estimation of recruitment rate and understanding of potential patient-centred primary and secondary outcome measures for the definitive trial. The planned recruitment for the cRCT is 324 participants.

**Ethics and dissemination:**

The trial received favourable ethical opinion from West Midlands—Black Country Research Ethics Committee (reference: 20/WM/0061) and approval from the Health Research Authority (IRAS number: 239324). Informed consent is not required for SDD intervention or anonymised data collection but is sought for investigations as part of the study, any identifiable data collected and monitoring of medical records. Results will be disseminated via publications in peer-reviewed medical journals.

**Trial registration number:**

ISRCTN40310490.

Strengths and limitations of this studyThe study will examine the processes that are important in a future clinical trial of Selective Decontamination of the Digestive tract (SDD) in the paediatric intensive care unit (PICU) setting.The study uses a GMP-certified commercial SDD preparation under licence from the George Institute, Australia (Verita Pharma Pty, Australia).The study will evaluate the perspective of parents and the views of stakeholders including caregivers and the multi-disciplinary team on the processes needed to undertake a trial of SDD in the PICU.The use of SDD-enhanced infection control requires it to be implemented unit-wide, along with the support of local microbiology, pharmacy and infection control teams for delivery and monitoring in sites randomised to implement it.This is a pilot study, so is not designed to assess effectiveness of the intervention; the study outcomes will inform the feasibility of a future trial based on clinical outcomes.

## Introduction

In critically ill children, healthcare-associated infections (HCAIs) are a major cause of morbidity and mortality, with a reported prevalence of 7%–14%.^1–5^ HCAIs can develop either as a direct result of healthcare interventions such as medical or surgical treatment, or from being in contact with a healthcare setting. In the critical care setting, the high use of invasive devices such as endotracheal tubes, vascular and urinary catheters increase the risk of secondary infection by opportunistic organisms. In particular, respiratory HCAIs (ventilator associated pneumonia, VAP) may occur with spread of commensal and other organisms from oro-pharyngeal and upper gastrointestinal compartments into the lungs.^4 5^

Evidence from adult intensive care studies suggests that using Selective Decontamination of the Digestive tract (SDD) alongside standard infection control measures reduces mortality and VAP.^6 7^ It has been shown that the use of SDD influences the microbiological ecology of the unit, thereby reducing incidence of HCAIs in both exposed and non-exposed patients. Despite this, SDD has not been routinely adopted due to concerns that it may promote antimicrobial resistance.^6 8^ Recent ecological studies conducted in adult intensive care have found that SDD was associated with a reduction in antibiotic utilisation^9–13^; two large cluster randomised controlled trials (cRCTs) have been recently undertaken to further evaluate the clinical effects of SDD in adult intensive care. One reported no change in the incidence of blood stream infections, but the incidence of ventilator acquired pneumonia and overall antimicrobial use have not yet been reported.^14^ Another large-scale multicentre study using the same formulation as the Paediatric Intensive Care and Infection Control (PICnIC) study has recently completed enrolment of critically ill adults in Australia, Canada and the UK.^15^

SDD has yet to be compared directly with modern infection control protocols within the paediatric intensive care unit (PICU) population. The only trial data suggest a reduction in incidence of VAP but not mortality, however the study was underpowered and the observed mortality was very low.^16^ Therefore, a clinical trial comparing SDD with standard infection control methods is required. Given the paucity of data describing the use of SDD in PICU and to establish the appropriate safety and ecological monitoring protocols, it is first imperative to establish whether a large, multicentre trial is feasible.

The PICnIC pilot study is a feasibility study designed to determine whether it is possible to conduct a cRCT of SDD in critically ill children who are likely to be ventilated for >48 hours, and to explore and test the acceptability of key components of the study to healthcare professionals and families of patients.

## Methods and analysis

### Aim

To determine whether it is feasible to conduct a multicentre trial in critically ill children comparing SDD with standard infection control procedures.

### Objectives

To test the ability to randomise PICUs to either control or intervention.To test the willingness and ability of healthcare professionals to screen and recruit eligible children.To estimate the recruitment rate of eligible children.To test adherence to the SDD protocol (including tolerance and application of a standardised SDD paste and suspension in a paediatric population).To test the procedures for assessing and collecting selected clinical and ecological outcomes and for adverse event (AE) reporting.To assess the generalisability of the study.To explore parent and healthcare professional views on the acceptability of the proposed trial, including recruitment and consent procedures and patient centred outcomes

### Study setting

Six PICUs based in England, UK with a diverse geographical/demographic population representative of national (UK) PICU activity and size.

### Design

External pilot, parallel group cRCT with integrated mixed-methods study. After a 1-week pretrial ecology surveillance period, recruitment to the cRCT will run for a period of 18 weeks, comprising: (1) baseline control period (‘period 1’—weeks 2–9); (2) mid-trial ecology surveillance period (week 10) and (3) intervention period (‘Period 2’—weeks 11–19). On completion of period 2, an additional 1-week post-trial ecology surveillance period will be carried out (figure 1). Sites will be randomised 1:1 by the trial statistician using computer-based randomisation, to either continue to deliver usual care or commence delivery of the intervention (SDD) in period 2 (figure 2).

**Figure 1 F1:**
[figure not shown]
Trial design. SDD, Selective Decontamination of the Digestive.

**Figure 2 F2:**
[figure not shown]
Trial schema of eligibility, site randomisation, study intervention, ecology surveillance, embedded mixed-methods study, follow-up. PICANet, Paediatric Intensive Care Audit Network; PICU, paediatric intensive care unit; SDD, Selective Decontamination of the Digestive.

### Screening

Potentially eligible patients presenting to the participating unit will be screened against the inclusion/exclusion criteria by the local clinical team, supported by the site research team. Screening Logs will record the reason patients are eligible but are subsequently not enrolled.

### Eligibility: ecology surveillance periods

#### Inclusion criteria

All patients admitted to the PICU, regardless of ventilation status, during any of the three ecological surveillance periods.

#### Exclusion criteria

None.

### Eligibility: period 1 and period 2

#### Inclusion criteria

>37 weeks corrected gestational age to <16 years.Receiving invasive mechanical ventilation, expected to last at least 48 hours.Expected to remain on invasive mechanical ventilation until the day after tomorrow (from time of screening).

#### Exclusion criteria

Known allergy, sensitivity or interaction to polymyxin E (colistin), tobramycin or nystatin.Known to be pregnant.Death perceived as imminent.

### Microbiology sampling

#### Samples taken

Nasopharyngeal.Stool/rectal swabs.Urine (if clinically indicated).Sputum/secretions from the endotracheal tube (If clinically indicated).Wound swabs, if present (if clinically indicated).

During the designated ecology surveillance periods, samples will be taken on admission and then taken on a Friday, if the patient has not had samples taken in the previous 48 hours.

During periods 1 and 2, samples will be taken on admission and then twice weekly until discharge. For patient stays of less than 7 days, samples should be taken on the day of discharge.

### Trial intervention

During the Ecology Surveillance periods, period 1 and for sites randomised to usual care in period 2, there is no intervention. Patients will receive all standard infection control measures (per the site’s specific policies) but will receive no study specific intervention.

For sites randomised to the intervention in period 2, it will form part of the standard infection control strategy in the participating PICU. In addition to usual care, an SDD-enhanced infection control regimen will be delivered to all eligible patients using a Good Manufacturing Practice (GMP)-certified commercial SDD preparation under licence from The George Institute, Australia (Verita Pharma Pty, Australia). (Within online supplemental file 1, online supplemental table 1) for SDD administration details, (online supplemental tables 2 and 3) for composition and characteristics of SDD, (online supplemental tables 4 and 5) for SDD formulation, online supplemental appendix 1 for GMP licence, online supplemental appendices 2–8 for SDD stability data and online supplemental appendix 9 for PICnIC labels). Dosing of the SDD suspension will be calculated according to age (table 1):

10.1136/bmjopen-2022-061838.supp1Supplementary data

**Table 1 T1:** SDD suspension dosing

	0–4 years	5–12 years	≥13 years
Polymyxin E (Colistin)	25 mg	50 mg	100 mg
Tobramycin	20 mg	40 mg	80 mg
Nystatin	0.5×106 IU	1×106 IU	2×106 IU
	2.**5** mL	**5** mL	10 mL

SDD, Selective Decontamination of the Digestive.

A 6 hourly topical, application of a pea-sized (0.5 g) SDD paste containing 2% polymyxin E (colistin), 2% tobramycin and 2% nystatin to the buccal mucosa and oropharynx.A 6 hourly administration of SDD suspension administered via the most proximal feeding tube into the stomach containing polymyxin E (colistin), tobramycin and nystatin.

SSD preparations will be distributed by the manufacturer in temperature-controlled (2°C–8°C), patient specific kits to the participating hospital pharmacies. Each kit contains a 5-day supply of SDD treatment which includes a bottle of SDD suspension powder for reconstitution and 20×1 mL syringes containing Oral Paste. When a kit is allocated to a patient and the SDD powder is reconstituted into suspension, the kit can be stored at room temperature (≤27°C) for up to 5 days. SDD treatment should be started within 6 hours of the patient being identified as eligible and continue for a maximum of 30 days (treatment period).

Treatment will continue until the patient is extubated or no longer mechanically ventilated (in tracheostomised patients). Patients subsequently reintubated (either during this PICU admission or readmission to PICU from another inpatient area) during the treatment period will restart the intervention. All other usual care will be provided at the discretion of the treating clinical team.

### Consent procedures

Children who are eligible for PICnIC will often become so during a period of life-threatening illness. This is a stressful time for parents/guardians during which time there are ethical concerns both about the burden placed of trying to understand the trial and their ability to provide informed consent.^17^

Posters displayed throughout the PICU will explain ecology sampling procedures and invite parents/guardians to have further discussions with research staff. The SDD intervention will be delivered, in additional to standard infection control policies, to all eligible patients in sites randomised to the SDD intervention during period 2. Research staff will not seek individual consent for this. This approach is in line with guidance from the Ottawa Statement on the ethical design and conduct of cRCT.^18 19^ (See online supplemental file 2) for poster and consent forms).

10.1136/bmjopen-2022-061838.supp2Supplementary data

Consent will be required for:

Any additional study-specific samples to be taken, stored and analysed prior to being taken solely for the study and not as part of routine care.Identifiable data collected and processed for participation in the mixed methods aspects of the study (questionnaire and interview).Monitoring of medical records.

Consent will not be required for:

Samples taken as part of routine care (eg, admission samples).Anonymised data collection and processing from routine sources.Delivery of SDD. For PICUs randomised to the intervention during period 2, all children meeting the eligibility criteria will receive SDD as the standard practice.

Children may be withdrawn from trial-specific data collection by the request of parents who decline participation in the research. All data collected up to the point of withdrawal will be retained and included in the study analysis.

If the patient has died, the parents/guardians will be approached for consent for the monitoring of medical records and identifiable data collected, and for the interview aspect of the study once established whether it is appropriate to approach for consent.

### Data collection

Detailed guidance for the collection of data will be provided in the trial-specific standard operating procedure. It will include:

Demographics.Date/time of commencing mechanical ventilation.Date/time identified as eligible.Antibiotic usage throughout admission (route, type, duration, frequency, dose).Date/time of final extubation.Details of any HCAI (confirmed/presumed).Date/time of PICU discharge.Date/time of hospital discharge.SDD delivery (dose for age, date time first dose, dose per day, change of dose, protocol deviation and reason for deviation)

No identifiable participant data will be required by the ICNARC Clinical Trials Unit (CTU) and all participant data will be stored securely. ICNARC is registered under the Data Protection Act (1998), and all ICNARC CTU staff have undergone data protection and International Conference on Harmonisation (ICH) Good Clinical Practice (GCP) training.

Patients will be followed up until discharge from a participating PICU. Data entered onto the secure trial database will undergo validation checks for completeness, accuracy and consistency of data. Queries on incomplete, inconsistent, or non-adherent data will be sent to the relevant PICU team for resolution.

Routine linkage will be made for all patients with the Paediatric Intensive Care Audit Network (PICANet) through the PICANet ID and trial number to obtain:

Baseline demographics and risk factors, including predicted risk of death.Secondary outcomes of critical care and acute hospital mortality, organ support received

### Safety monitoring

AE reporting will follow the Health Research Authority (HRA) guidelines on safety reporting in studies which do not use Investigational Medicinal Products.

AEs will be recorded during period 2, from enrolment until PICU discharge (including readmissions from other inpatient areas until 30 days from being identified as eligible). For patients receiving SDD intervention, only AEs deemed possibly, probably or definitely related to the trial intervention should be reported to ICNARC CTU, apart from NG tube blockages which should be reported even if not deemed related. For patients receiving usual care, only NG tube blockages will be reported.

The following events have been prespecified as potential AEs:

NG tube blockage.Choking on pasteAllergic reaction to SDD.

The following events are exempt for reporting as AEs or serious AEs (SAEs)

Deterioration of condition or death that is not related to the trial intervention.AEs of other drugs not specified in the protocol.

Any event classified as ‘severe’, ‘life-threatening’ or ‘fatal’ in severity is considered an SAE and must be reported to ICNARC CTU. If the SAE is evaluated by the chief investigator or clinical member of the Trial Management Group (TMG) as a related and unexpected SAE, the ICNARC CTU will submit a report to the Research Ethics Committee (REC) within 15 calendar days.

### Patient and public involvement

Caregivers of children admitted to PICU and a former patient were involved in prioritising the outcomes and designing the study protocol. Their input has continued with patient and public involvement (PPI) representatives on the study oversight panel. A patient representative (former PICU patient) is a coinvestigator and is an author of this manuscript.

### Outcome measures

As this is a pilot study, outcome measures for the study will be focused on assessing the feasibility of a larger scale definitive study.

The ability to randomise PICUs to either control or intervention will be assessed by the successful random assignment of three PICUs to the intervention without delay to subsequent phases of the trial.

The willingness and ability of healthcare professionals to screen and recruit eligible children will be assessed by the proportion of eligible children recorded on study screening logs successfully recruited to the pilot cRCT and the reported reasons for non-recruitment.

The potential recruitment rate for a future definitive cRCT trial of SDD-enhanced infection control in eligible children will be estimated by combining the proportion of eligible children recruited to the pilot cRCT with the size of the potentially eligible population (estimated from nesting the screening log data from participating PICUs within the national UK PICU data from PICANet).

Adherence to the SDD protocol will be assessed by the proportion of eligible children allocated to the intervention receiving (1) both elements and (2) each individual element of the SDD intervention, the number of days on which these elements were received relative to days eligible for the SDD intervention and the reported reasons for nonadherence.

Procedures for assessing and collecting selected clinical and ecological outcomes and for AE reporting will be assessed by the proportion of children with complete data for these outcomes including, for ecological outcomes, the proportion consenting to additional study specific sample collection.

Generalisability of the study results to all UK PICUs will be assessed by comparing baseline characteristics and outcomes for children recruited to the pilot cRCT with data from all potentially eligible children (receiving invasive mechanical ventilation for at least three calendar days) within participating PICUs and within all UK PICUs (from PICANet).

With the aim of understanding potential patient-centred primary and secondary outcome measures for the definitive cRCT, the following potential outcome measures will be reported:

HCAI (confirmed/presumed) and microbiology results (if positive sample).Hospital mortality.PICU mortality.Mortality within 30 days postenrolment.Length of hospital stay.Length of stay in PICU.Duration of mechanical ventilation.Organ support received.

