#### Analysis

An overview of the planned analyses for the PICnIC pilot study is provided below. The full statistical analysis plan will be lodged on the trial website ahead of database lock.

A Consolidated Standards of Reporting Trials flow diagram will be used to summarise the number and percentage of children screened, recruited and followed up. This will include the proportion of eligible children successfully recruited and the reported reasons for non-recruitment.

Recruitment to the pilot cRCT will be presented as a rate per site per week over the two recruitment periods, overall, by treatment group and by site. Potential reasons for variation in recruitment rates will be explored. The potential recruitment rate for a future definitive cRCT will be estimated by combining the proportion of eligible children recruited to the pilot cRCT with the size of the potentially eligible population (estimated from PICANet).

Baseline demographic and clinical data will be summarised overall and for each of the two treatment groups in each of the two time periods but not subjected to statistical testing.

The proportion of eligible children allocated to the intervention that received both elements and each individual element of the SDD intervention will be reported as well as the number of days on which these elements were received relative to days eligible for the SDD intervention. The reported reasons for nonadherence will be detailed.

Data completeness of clinical and ecological outcomes and for AE reporting will be summarised.

Patient characteristics for children recruited to the pilot cRCT will be compared with those for potentially eligible children within participating PICUs and within all UK PICUs.

Potential patient-centred clinical outcome measures for the definitive trial will be estimated and reported (proportion or mean and SD, and intracluster correlation). As a pilot cRCT, there will be no statistical testing for any of the summary measures. Comparisons between groups will be used to estimate the potential magnitude of the treatment effect; p values will not be calculated or quoted.^20^ To account for cluster randomisation, we will use multilevel logistic or generalised linear regressions in the above analyses.

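### The generalisability comparison sets children recruited on expected ventilation, about a quarter of them SDD-treated, against PICANet children selected on observed ventilation, so its outcome part is not like for like

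*Protocol article*

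**What the plan says.** **Who is recruited.** Under Eligibility: period 1 and period 2, Inclusion criteria, the ventilation conditions are forecasts: "Receiving invasive mechanical ventilation, expected to last at least 48 hours" and "Expected to remain on invasive mechanical ventilation until the day after tomorrow (from time of screening").

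**Who they are compared with.** Outcome measures defines the comparator as "all potentially eligible children (receiving invasive mechanical ventilation for at least three calendar days"), within participating PICUs and within all UK PICUs, from PICANet. This is ventilation received.

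**What is compared.** Outcome measures speaks of "comparing baseline characteristics and outcomes for children recruited to the pilot cRCT" with those of the comparator. It does not say which outcomes. Its list of potential outcomes for the definitive trial includes mortality, lengths of stay, organ support and "Duration of mechanical ventilation". Analysis describes the same comparison more narrowly: "Patient characteristics for children recruited to the pilot cRCT will be compared with those for potentially eligible children", with no mention of outcomes.

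**Who is treated.** Under Consent procedures, at intervention sites in period 2 "all children meeting the eligibility criteria will receive SDD as the standard practice". Sample size expects about 324 children, 90 of them receiving the intervention.

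Neither section limits the recruits in this comparison to children who reached three calendar days of ventilation, or to usual-care children.

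**The concern.** Assessing generalisability is one of the listed objectives. The comparison is informative only if a difference between recruits and comparator can be read as a difference between the children the trial reached and the children it is meant to represent. Two other sources of difference are built in.

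1. **Definition.** A recruit who is extubated or dies sooner than forecast stays in the recruited group, while a similar child is absent from the comparator. Conversely, a child not expected to stay ventilated, but who did, is in the comparator and could never have been recruited.
2. **Treatment.** Recruits at intervention sites in period 2 carry any effect of SDD into the recruited group's outcomes. The comparator is predominantly untreated, at least in the all-UK comparison.

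A reader of the pilot report could not separate either of these from selective recruitment. Ventilation duration is the most exposed outcome, since it is the variable on which the comparator is selected. Mortality is exposed because death before the third calendar day is excluded from the comparator by construction.

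**Working it through.** **Plan's own figures.** 6 PICUs × 3 per week × 18 weeks = 324, as stated. The usual-care group is 324 − 90 = 234. The half-width for a 20% outcome is 1.96 × √(0.2 × 0.8 / 234) = 0.051, agreeing with the stated ±5% after rounding (clustering ignored).

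**Share of recruits treated with SDD.** 90/324 = 27.8%. Design puts period 2 at weeks 11–19, which is nine weeks; 3 sites × 3 per week × 9 = 81, and 81/324 = 25.0%. That discrepancy is a separate matter. Either count gives about a quarter.

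**Effect of mixing in SDD.** If a share s is treated and SDD multiplies an event rate by RR, the pooled rate is 1 − s(1 − RR) times its untreated value. The documents give no RR, so these are assumed:

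| RR | s = 27.8% | s = 25.0% |
|---|---|---|
| 0.9 | 0.972 | 0.975 |
| 0.7 | 0.917 | 0.925 |
| 0.5 | 0.861 | 0.875 |

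**Effect of the definition: early endings among recruits alone.** Let f be the share of recruits ventilated for fewer than three calendar days. Recruited mean = (1 − f) × long-stay mean + f × short-stay mean. With assumed means of 8 and 1.5 days, f = 10% gives 0.9 × 8 + 0.1 × 1.5 = 7.35 days against 8.0 in the comparator, so recruits look shorter. For mortality even the sign is open. With f = 20% and 8% mortality in longer stays, assumed short-stay mortality of 2% gives 0.8 × 8% + 0.2 × 2% = 6.8%, and 15% gives 0.8 × 8% + 0.2 × 15% = 9.4%.

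**Effect of the definition: both flows together.** The simulation recruits every child who meets the forecast criteria, so recruitment is fully representative. Assumptions: log-normal ventilation time with log-SD 1 and median 2.5 or 4 days; start time uniform over the day, with the forecast made at that point; forecast error SD of 0, 0.5 or 1 on the log scale.

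| Median time, forecast error | Recruits under 3 calendar days | Comparator not meeting forecast | Median, recruits | Median, comparator |
|---|---|---|---|---|
| 2.5 d, 0 | 0% | 16% | 4.30 | 3.69 |
| 2.5 d, 0.5 | 5% | 21% | 4.31 | 3.69 |
| 2.5 d, 1 | 11% | 29% | 4.02 | 3.69 |
| 4 d, 0 | 0% | 10% | 5.46 | 4.92 |
| 4 d, 0.5 | 3% | 15% | 5.61 | 4.92 |
| 4 d, 1 | 6% | 23% | 5.62 | 4.92 |

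The gaps run from 4.02 − 3.69 = 0.33 to 5.62 − 4.92 = 0.70 days, and here recruits look longer. Part of this arises because 48 hours is stricter than three calendar days. With perfect forecasting and only the three-calendar-day rule in the forecast, the gap is zero (3.69 v 3.69; 4.92 v 4.92).

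**What matching on the observed rule does.** Limiting the simulated recruits to those with three or more calendar days gives medians of 4.30, 4.51 and 4.53 (v 3.69) and 5.46, 5.76 and 5.98 (v 4.92). The early endings are gone, but comparator children who never met the forecast remain, so a gap persists and can be wider.

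**The case against.** The strongest case against the point has four parts.

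- **The proxy is reasonable.** An audit dataset is unlikely to hold a clinician's forecast, and three calendar days is close to the second inclusion criterion. The article openly calls these children potentially eligible. This stands for counting the population; it does not make the outcome comparison like for like.
- **The outcome comparison may be small or absent.** Analysis mentions patient characteristics only, and Data collection names only mortality and organ support as outcomes obtained through PICANet. SDD cannot change baseline characteristics, and excluding children whose death seems imminent limits early deaths among recruits. This narrows the point to outcomes, and ventilation duration or length of stay matters only if compared. But Outcome measures does say outcomes, so the two sections need reconciling.
- **The remedy belongs in the SAP.** Extra columns often do. Here, however, the article itself fixes a comparator and a recruited group that do not match.
- **The stakes are modest.** It is one descriptive objective of a pilot, without testing, and no progression rule in the article hangs on it. This stands.

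A reader might also think it wrong that, within participating PICUs, the comparator contains the recruits. It is not: whether recruits resemble the whole eligible population is a legitimate question, and non-recruitment is examined separately through the screening logs. Nor can one use the planned 3 recruited of 4.5 eligible to say that a true difference shrinks to one third. That identity needs recruits to be a subset of the comparator, and under the present definitions some are not.

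**Conclusion.** The point holds for the outcome part of the generalisability comparison. As written, it mixes a difference in definition, and any SDD effect in about a quarter of recruits, with representativeness. Outcomes can differ when recruitment is fully representative.

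A reader might infer that recruits will look shorter-ventilated, or different by a set percentage. The documents do not support that. They give no share of recruits ventilated under three calendar days, no forecast accuracy and no SDD effect. Counting only early endings makes recruits look shorter; counting both flows made the simulated medians longer, by 0.3 to 0.7 days. These figures show that the effect need not be negligible; they are not estimates for this trial.

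For baseline characteristics the distortion is likely smaller, and it comes from the definition alone. This is a worthwhile, inexpensive improvement to a stated objective, and it does not affect trial conduct or safety.

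**What to change.** For this comparison only:

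1. Apply the observed three-calendar-day rule to recruits, derived from PICANet through the planned linkage so that both groups use one source and definition, and show all recruits in an adjacent column.
2. Make the outcome comparison with usual-care recruits.
3. Reconcile Outcome measures with Analysis: state whether outcomes are compared and, if so, which.

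Step 1 removes the early endings and makes the matched recruits a subset of the observed-ventilation population in participating units. It does not remove comparator children who never met the forecast, so any remaining gap should be reported as reflecting the entry criteria as well as recruitment. The adjacent column lets readers see what the rule does.

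The cost is wording, a little programming on data already collected or linked, and a smaller matched group. If 11% of recruits were dropped (the largest simulated share), 234 usual-care recruits would become 0.89 × 234 ≈ 208, and the half-width for a 20% outcome would go from 5.1 to 1.96 × √(0.16/208) = 5.4 percentage points. The change can go into the full analysis plan, which the article says will be lodged before database lock.
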